## Abstract

**Background:**

Tobacco smoking remains one of the biggest public health threats. Smartphone apps offer new promising opportunities for supporting smoking cessation in real-time. The social context of smokers has, however, been neglected in smartphone apps promoting smoking cessation. This randomized controlled trial investigates the effectiveness of a smartphone app in which smokers quit smoking with the help of a social network member.

**Methods:**

This protocol describes the design of a single-blind, two-arm, parallel-group, intensive longitudinal randomized controlled trial. Participants of this study are adult smokers who smoke at least one cigarette per day and intend to quit smoking at a self-set quit date. Blocking as means of group-balanced randomization is used to allocate participants to intervention or control conditions. Both intervention and control group use a smartphone-compatible device for measuring their daily smoking behavior objectively via exhaled carbon monoxide. In addition, the intervention group is instructed to use the SmokeFree Buddy app, a multicomponent app that also facilitates smoking-cessation specific social support from a buddy over a smartphone application. All participants fill out a baseline diary for three consecutive days and are invited to the lab for a background assessment. They subsequently participate in an end-of-day diary phase from 7 days before and until 20 days after a self-set quit date. Six months after the self-set quit date a follow-up diary for three consecutive days takes place. The primary outcome measures are daily self-reported and objectively-assessed smoking abstinence and secondary outcome measures are daily self-reported number of cigarettes smoked.

**Discussion:**

This is the first study examining the effectiveness of a smoking cessation mobile intervention using the SmokeFree Buddy app compared to a control group in a real-life setting around a self-set quit date using a portable objective measure to assess smoking abstinence. Opportunities and challenges with running studies with smoking participants and certain design-related decisions are discussed.

**Trial registration:**

This trial was prospectively registered on 04/04/2018 at ISRCTNregistry: ISRCTN11154315.

## Background

Smoking remains one of the leading preventable causes of premature death worldwide [1]. Smokers who smoke approximately 16 cigarettes per day lose about 11 min of their lifetime per cigarette smoked [2]. Additionally, smoking is an important risk factor for serious health problems and life-threatening diseases such as lung cancer, coronary heart disease and stroke [1]. Despite the knowledge about the negative consequences of smoking, in 2016 every fourth person aged 15 and older smoked in Switzerland [3]. High relapse rates indicate that quitting smoking is a major challenge [4]. The core of relapse prevention is to strengthen the capability to manage high-risk situations (e.g., cue-induced cravings [5, 6]). Although many evidence-based smoking cessation interventions exist (e.g., behavioral counselling, medications, nicotine replacement therapy [7]), the majority of smokers quit unassisted without the help of pharmacological aids or other interventions [8, 9]. The accessibility and availability of mobile technology (e.g., mobile phones/smartphones) offers new promising opportunities for cost-effective interventions in everyday life [10]. As most relapses occur within the first weeks after the quit attempt [4, 11], such interventions have the potential to deliver support when it is most needed [11, 12].

### Smartphone apps to promote smoking cessation

In 2016 mobile-broadband networks reached 84% of the global population [13]. Among a sample of US and UK smokers the prevalence of smartphone ownership with internet access with over 75% was high [14]. In the context of smoking cessation, there are already numerous studies on text messages based interventions using mobile phones [15]. The efficacy of these interventions is tentatively confirmed as positive effects were found up to 6 months after quitting smoking [16, 17]. In contrast, there are far fewer smartphone app-based smoking cessation intervention studies in daily life [18]. Due to the high prevalence of smartphone usage, delivering health promotion interventions using smartphone apps is a promising approach, especially because of the proximity to users, cost effectiveness, location independence, possibility of tailoring and providing instant interactive support [19–21].

First studies on smartphone apps and smoking cessation provide good evidence that apps are a useful tool to promote the implementation of the intended behavior (c.f., [10, 22]). For example, preliminary results of the SmokeFree28 app showed higher cessation rates for 28 days than unaided cessation [23]. Also, in a RCT of the smartphone app REQ-Mobile smokers who used the app showed higher abstinence rates at 30 days compared to smokers who did not use the app [10]. Furthermore, in another RCT smokers who received a smartphone app to quit were more likely to be continuously abstinent at 1 month, 3 months and 6 months after quitting [22]. All those apps assessed smoking abstinence by self-report only.

In a content analysis of smartphone apps for smoking cessation, calculator apps were the most common category (38.8% of all apps), followed by hypnosis apps (17.3%), rationing apps (15.3%), trackers (12.2%), informational apps (6.1%), games (3.1%) and lung health testers (2.0%) [20]. In line with these findings, another content analysis of Android smoking cessation apps also found that apps predominantly provide simple tools, as for example calculators, calendars, trackers or distractors [24]. Most available apps used very little evidence-based content to support quit attempts [19]. In approximately 55% (*n* = 75) of the apps no behavior change techniques (BCTs [25];) were present [19]. Apps rarely referenced smokers outside of the app to a quit helpline or provided opportunities to reach out for social support from a social network member [20]. Of 225 rated Android apps only 6 (2.7%) had also content regarding social support for smokers [24]. However, one of the key recommendation of the clinical practice guideline Treating Tobacco Use and Dependence [7] is to deliver social support in individual, group or telephone counseling settings. External resources such as social support seem promising in helping smokers to quit and might buffer the daily stress smokers experience while quitting [4, 11, 26].

### Social support and smoking cessation

Social support comprises resources provided to a person in need and can include the following functions: emotional (e.g., comforting, encouraging) and instrumental (practical help or assistance) [27, 28]. It can be distinguished into a recipient’s retrospective report of support received (i.e., *received* support), a provider’s retrospective report of support given (i.e., *provided* support), and the perceived prospective potential access to social support resources (i.e., *perceived support*) [27–29]. There is evidence from longitudinal, prospective studies that higher received social support from a network member is related to higher abstinence rates (e.g., [30]). In a recent intensive longitudinal mobile phone-based study with single-smoker couples the fine-grained temporal dynamics of daily social support and daily number of cigarettes smoked was investigated in the process of quitting [26]. Increases in received emotional and instrumental support were related to less smoking, and effects were more pronounced after a self-set quit date when support is most needed. Also, support provided from the non-smoking romantic partner was associated with less smoking [26]. Consistent with these findings, in another intensive longitudinal mobile phone-based study with dual-smoker couples, received emotional and instrumental support was related to less smoking after a joint self-set quit date [31]. For men only, female partner’s provided emotional and instrumental support was also related to fewer cigarettes smoked in dual-smoker couples [31].

Up to date, several intervention studies exist to foster social support [32]. However, results on the effectiveness are mixed [33, 34]. In a review investigating RCTs that compared smokers who received an intervention to enhance peer or partner support with smokers who did not receive the support intervention, the effectiveness of the social support interventions was not clearly given [35]. In another review there was also lack of evidence regarding the efficacy of the use of buddies in community interventions [11]. For example, in a study examining the effectiveness of a social support intervention with a buddy in a group treatment program to aid smoking cessation, smokers in the buddy condition (smokers were paired with another participant to provide mutual support) were no more likely than smokers in the control condition to stay abstinent at one, four or 26 weeks [36]. Thus, it seems that buddy systems so far have been unable to improve abstinence rates of participants in group treatment programs.

Findings from intervention studies could, thus, not demonstrate the assumed effectiveness of partner or peer support on smoking cessation, supposably because these interventions were not successful in increasing social support in the first place [11, 37, 38]. One of the problems associated with this could be that these buddy systems often rely on unacquainted buddies, not persons from one’s own personal social network. Moreover, buddies need instructions on how to support smokers during a quit attempt to ensure high quality of social support. The ideal timing of support seems relevant; that is, when in the process of smoking cessation social support is most helpful for smokers [11, 39]. This emphasizes that future intervention studies enhancing social support should take place in smoker’s everyday life and social support should be available directly when smokers need it. This issue can be addressed by applying ecological momentary interventions (EMI [40];) that are characterized by the delivery to people as they go about their everyday lives in combination with momentary ambulatory assessments [40]. EMI’s can be used to stimulate processes that take place in everyday life, as for example social support. Thus, a smartphone app for targeting social support in the context of smoking cessation would allow not only to address the aspect of timing but could also provide the target person with tailored social support while quitting. There is first evidence from a randomized pilot trial comparing automated text-messaging support (control group) with automated text-messaging support plus personalized texts from a peer mentor who formerly smoked (peer-mentor group) that smoking abstinence at 3 months was higher for the group with peer mentors compared to the control group [41]. However, the role of social support from a network member via a smartphone app has not yet been investigated in the context of smoking cessation. The present study investigates the efficacy of such a smartphone app, the SmokeFree Buddy app, connecting a smoker with a freely chosen support buddy to promote smoking cessation in smoker’s everyday life using a randomized controlled trial (RCT).

### The SmokeFree buddy app

As part of the tobacco prevention campaign in Switzerland the Federal Office of Public Health (FOPH) and its partners developed a smartphone app –the SmokeFree Buddy app - to encourage smokers’ intention to quit and to offer social support interactively from a self-chosen person (buddy) while quitting smoking. The SmokeFree Buddy app was developed from experts based on the empirical and theoretical evidence of social support from a social network member for smoking cessation. Mobile interventions have the potential to intervene at any time, in a tailored manner and during actual experiences in people’s everyday life [40]. The SmokeFree Buddy app, thus, aims at enabling smokers to quit with the help of a self-chosen buddy from one’s social network and offers the possibility of enhancing social support resources and availability directly after a self-set quit attempt in smoker’s everyday life. The buddy then gets instructed via the smartphone app on how to support the smoker during his/her quit attempt. In addition to self-reported smoking behavior the present RCT uses an objective device to assess smoking abstinence via a “smokerlyzer” with a corresponding smartphone app and is therefore, the first study assessing smoking abstinence objectively on a daily basis.

A general criticism on standard RCT’s is that the level of longitudinal assessment is usually on a macro-time level (e.g., baseline and a 1 month follow-up). This is also the case for intervention studies on social support in the context of smoking cessation (i.e., [11, 37, 38]). However, relatively little is known on when an intervention reaches its effect and what time window would be appropriate to capture it. As such, the choice for the follow-up time points is often made on an arbitrary basis. By using micro-time assessments (e.g., daily) during an ongoing intervention, it is possible to answer questions on how an intervention effect unfolds over time, when it reaches its maximal effect and whether it is maintained or levels off quickly [42]. Moreover, it allows investigating how people respond differently to the intervention. In the present study, we combine micro-time and macro-time assessments by using an intensive longitudinal intervention design with three end-of-day diary periods across 6 months. The 6 months time period was chosen for better comparability with previous studies using a six-month follow-up.

### Aims of the present study

This study aims to test the effectiveness of a smoking cessation mobile intervention using the SmokeFree Buddy app compared to a control group in a real-life setting around a self-set quit date, and to examine the hypothesized mediating mechanisms. More specifically, the research aims are the following: 1) Is the SmokeFree Buddy app an effective intervention to promote daily abstinence rates and to reduce daily number of cigarettes smoked in adult smokers at the self-set quit date, 3 weeks (end of intervention) and 6 months later in comparison to a control group? The primary outcome measures are daily self-reports of smoking abstinence (subjective) and daily smoking abstinence using exhaled carbon monoxide (objective). Daily self-report of number of cigarettes smoked serves as secondary outcome measure. 2) What are the trajectories over time of daily smoking abstinence rates and daily number of cigarettes smoked in the intervention compared to the control group? 3) Does the SmokeFree Buddy app increase social support and self-regulatory processes in daily life and do these constructs serve as mediating mechanisms explaining the effect of the SmokeFree Buddy app? Hypothesized mediators are daily self-reports of intensity and quality of social support, self-efficacy and action control. For the specific hypotheses please see the trial registration: ISRCTN11154315 (10.1186/ISRCTN11154315). This trial was prospectively registered on 04/04/2018.

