### Statistical analysis

Upon completion of data collection, data will be cleaned and prepared for data analyses. Primary and secondary outcome variables and mediating mechanisms will be checked for distribution, outliers and missing patterns, and appropriate steps will be taken where necessary (cf., [57]). All analyses follow intention-to-treat principles, taking advantage of all available data points. Low levels of missings will be expected, with previous studies showing high completion rates (> 90%, e.g., [26]). Intermittent missing data will be handled by maximum likelihood (MI) estimation. Participants who completely drop out of the study will be treated as smokers. Preliminary analysis will include a randomization check to test for baseline differences between intervention and control participants. For the main data analysis, we will use multilevel modeling to account for the nested structure of daily measures within individuals [58]. To examine the first research question on the effects of the intervention using the daily diary, a set of generalized linear mixed models will be performed in SPSS and R. Daily smoking abstinence will be modeled as a function of time group and group by time, testing group differences at the quit date (model 1) and 3 weeks later (model 2) by centering the time variable accordingly. Model 3 will separately test group differences 6 months later. For the primary outcomes of subjectively and objectively reported smoking abstinence (dichotomous), we will use mixed logistic regression analyses. For the secondary outcome of subjectively reported number of cigarettes smoked, a count variable, we will use a negative binomial model with zero inflation [59, 60]. To test the third research question on the mediating mechanisms of the intervention effect, we will use a multilevel approach to mediation analysis based on multilevel structural equation models [61, 62].

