### Power analysis

To secure adequate power for the main analysis of the intervention effect on smoking abstinence at the quit date, 3 weeks and 6 months later, we performed a priori sample size calculations using the G*Power program [63]. Based on a power of 0.80 and a two-tailed Type 1 error probability of .05, a total sample size of *N* = 128 is suitable to detect a 24% difference in smoking abstinence for the intervention group, drawing on meta-analyses of mobile-phone interventions on short and long-term smoking abstinence (RR’s between 1.7 and 2.1 [16, 17];). We assumed an abstinence rate of 27% in the control group 6 months after the self-set quit date, based on own previous studies using a highly comparable, albeit correlational, design with daily diaries around a self-set quit date in smokers and their romantic partners [64, 65]. Moreover, attrition rates between 20% (e.g., [31]) 6 months after the self-set quit date, or below 30% [15] have been reported. Thus, assuming an attrition rate of 25%, the targeted sample size is *N* = 160 smokers (*n* = 80 per group) and an additional *N* = 80 buddies.

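### Six primary contrasts share one two-sided .05 and one power of 0.80, and the article gives no rule for which of them decides whether the app works

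*Protocol article*

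**What the plan says.** In the protocol article, Aims of the present study, the first research aim is a single effectiveness question covering three times: "at the self-set quit date, 3 weeks (end of intervention) and 6 months later in comparison to a control group". The same paragraph gives two primary outcomes of equal rank: "The primary outcome measures are daily self-reports of smoking abstinence (subjective) and daily smoking abstinence using exhaled carbon monoxide (objective". For the specific hypotheses it refers to the trial registration.

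Statistical analysis assigns a group test to each time. Two come from the daily diary model, "testing group differences at the quit date (model 1) and 3 weeks later (model 2) by centering the time variable accordingly". The third stands apart: "Model 3 will separately test group differences 6 months later". Both outcomes are analysed this way: "For the primary outcomes of subjectively and objectively reported smoking abstinence (dichotomous), we will use mixed logistic regression analyses".

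Power analysis treats the three times as one target, the "main analysis of the intervention effect on smoking abstinence at the quit date, 3 weeks and 6 months later". The inputs are given once: "Based on a power of 0.80 and a two-tailed Type 1 error probability of .05". The result is that a total of "128 is suitable to detect a 24% difference in smoking abstinence for the intervention group", with an assumed control abstinence rate of 27% at 6 months.

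None of these sections says which outcome or time decides the question, in what order the tests are read, whether both outcomes must agree, or whether the test level is adjusted.

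**The concern.** A two-sided .05 and a power of 0.80 describe a single test. Here they are attached to a main analysis made of two outcomes at three times. Without a decision rule, the chance of wrongly concluding that the groups differ, and the chance of detecting a real effect, both depend on how the six results are combined after they are seen.

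Disagreement between the outcomes is a real possibility. The Background notes that the earlier app studies it describes relied on self-report only, and presents daily CO measurement as this trial's advance, so the two measures are not treated as interchangeable. If self-report shows a difference and CO does not, or the effect appears at 3 weeks and not at 6 months, the article does not say what the answer to the first aim is.

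**Working it through.** **1. Count the contrasts.** Two primary outcomes (Aims) × three times, models 1 to 3 (Statistical analysis) = 6. The secondary outcome, the trajectories and the mediators are not counted.

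**2. Reproduce the sample size.** Inputs from Power analysis: control 0.27, difference 0.24, hence intervention 0.51; two-sided .05; power 0.80. Allocation is 1:1 (Randomization). With pooled variance and no continuity correction, the mean rate is 0.39 and

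n per group = [1.960 × √(2 × 0.39 × 0.61) + 0.842 × √(0.27 × 0.73 + 0.51 × 0.49)]² / 0.24² = (1.352 + 0.563)² / 0.0576 ≈ 63.6, rounded up to 64.

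That gives N = 128 with power 0.802. The article's figure is reproduced as one comparison of two proportions at one time.

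**3. Error rate if any one of six suffices at .05 each.** Both conditions are assumptions.
- Independent tests, either direction: 1 − 0.95⁶ = 0.265.
- Independent tests, results favouring the app only: 1 − 0.975⁶ = 0.141.

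The six tests will be correlated, and the article gives no correlations. Six normal test statistics were therefore simulated (400,000 to 1,000,000 draws). The correlation between different outcomes at different times was set to the product of the two assumed values.

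| Between outcomes | Between times | Any false difference | Favouring the app |
|---|---|---|---|
| 0 | 0 | 0.265 | 0.141 |
| 0.5 | 0.3 | 0.237 | 0.120 |
| 0.8 | 0.3 | 0.207 | 0.104 |
| 0.8 | 0.5 | 0.190 | 0.095 |
| 0.9 | 0.5 | 0.173 | 0.086 |
| 0.9 | 0.7 | 0.151 | 0.075 |
| 0.95 | 0.8 | 0.124 | 0.062 |

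Against .05, the either-direction column runs from 0.124/0.05 = 2.5 to 0.265/0.05 = 5.3 times. The last column should be compared with the .025 that a two-sided .05 test allows in one direction: 0.062/0.025 = 2.5 to 0.141/0.025 = 5.6 times.

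**4. Error rate under a stricter rule.** If both outcomes must be significant in the same direction at the same time, at any of the three times, the chance of a false result is about 0.01 to 0.09. That range covers correlations of 0.3 to 0.9 between outcomes and 0.2 to 0.8 between times. About half of it favours the app.

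**5. Power if more than one test must succeed.** Suppose each test had power 0.80 on its own. Requiring both outcomes at one time gives 0.80² = 0.64 if they are independent. Requiring all six gives 0.80⁶ = 0.262. Positive correlation raises these figures, but joint power reaches 0.80 only if the tests are perfectly correlated.

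**6. Cost of splitting the level.** Bonferroni over six uses .05/6 = .00833. At 64 per group, power falls from 0.80 to 0.56. Restoring 0.80 would need 198 evaluable participants instead of 128.

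**The case against.** The strongest reply is that the article condenses a fuller protocol, that it sends the reader to the registration for specific hypotheses, and that multiplicity handling is commonly left to an analysis plan. An ordering could sit in either place. This stands in part: the point can only be that this article contains no rule, not that none exists. It does not remove the point, because the article does not leave the matter open. It fixes two primary outcomes, three times and three models, and attaches one error rate and one power to all three times together. Those figures fit only a single named test.

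A second reply is that a reader might infer from the text that any one significant result of six may be reported as effectiveness. The article never says so. It lists self-report and CO together, and requiring both would give a much lower error rate (step 4). This stands: the error rate is undetermined, and 0.12 to 0.26 describes one possible reading. Likewise, testing each contrast at .05 is inferred from the sample size inputs; Statistical analysis states no level.

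A third reply concerns direction. A reader might infer that the chance of falsely declaring the app effective is three to five times .05. The documents do not support that. Figures of that size count false differences in either direction, and those favouring the app are about half. A ratio of roughly that size holds for pro-app errors only against the one-directional .025.

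Finally, the article explains why it studies three times: to learn when an effect appears and whether it lasts. That justifies measuring at all three, but not leaving the confirmatory claim unranked.

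**Conclusion.** The point holds in a limited form. The article asks one effectiveness question over six unranked primary contrasts and gives them a single-test .05 and 0.80. Those figures do not carry over to the six contrasts when any one result suffices, nor when both outcomes or all times must succeed.

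Under the two assumptions of .05 per test and any one sufficing, at least one false significant difference has a chance of about 0.12 to 0.26. A false result in favour of the app has a chance of about 0.06 to 0.14, against a nominal .025. The ranges rest on assumed correlations. Self-report and CO abstinence are probably highly correlated, which points to the lower half. Under a both-must-succeed rule the error problem shrinks and the problem becomes one of power. Whether a rule exists in the registration or an analysis plan cannot be judged from the article.

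**What to change.** Before unblinding, add one paragraph to the analysis plan that:
- names one confirmatory test at two-sided .05. CO-assessed abstinence at 6 months is the natural choice, because the sample size uses the 6-month control rate and the Background gives comparability with earlier studies as the reason for a 6-month period;
- lists the other five contrasts in a fixed order, each tested at .05 only if all before it were significant, with everything after the first non-significant result reported as descriptive. The order is the sponsor's choice;
- states that the .05 and the 0.80 apply to the lead test.

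If the registration already contains such an order, citing it and aligning the power statement with it would be enough.

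The change needs no extra participants and takes no power from the lead test. The price is that success can no longer be claimed from any single one of the six. Bonferroni over six would keep that option, but at 64 per group it would cut power from 0.80 to 0.56.
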